# INTRODUCTION

The World Health Organization (WHO) defines latent Mycobacterium tuberculosis infection (LTBI) as a state of persistent immune response to stimulation by Mycobacterium tuberculosis antigens without evidence of clinical manifestations of active tuberculosis (TB). It is estimated that a quarter of the world population is infected by this bacterium. Despite the absence of symptoms, there is a risk of these patients developing active TB, especially in the first two years after the primary infection worsened in the case of immunosuppression. Activation occurs in 5-10% of cases (LEITE-JÚNIOR, 2017).

Thus, the evaluation of contacts of TB cases is of relevant importance for the screening of LTBI, which requires proper diagnosis and treatment, with the aim of preventing the development of active TB in the future, also interrupting the disease transmission cycle. In Brazil, the National Tuberculosis Control Program/Ministry of Health (PNCT) considers any person who lives in the same environment as the index case as contact at the time of diagnosis of TB. Contacts under the age of five, people with HIV and people with high-risk conditions should be considered a priority in the process of evaluating contacts and treating LTBI (BRASIL, 2017).

The drug Isoniazid is used worldwide for the treatment of LTBI and reduces the risk of illness by 60 to 90%, depending on adherence and duration of treatment (WHO, 2015). As recommended by the Health Surveillance Guide (2017), the current regimen indicated and available for the treatment of LTBI is with the presentation of Isoniazid 100mg in a dosage of 5 to 10 mg/kg/day (maximum dose of 300mg/day) in 270 doses that should be taken from 9 to 12 months (BRASIL, 2017). However, from 2018, Isoniazid 300mg will also be made available to the health network, which should be incorporated by the services. In other words, there will be two presentations of Isoniazid (100mg and 300mg) in the units studied to be used in the treatment of LTBI. Studies carried out by FIOCRUZ indicate that the two formulations have bioequivalence (Daher et al, 2015).

The two presentations of Isoniazid (100mg and 300mg) will be available to be used as needed depending on the weight range of adults and children. Since overdose of Isoniazid can lead to severe drug hepatitis and death, correct use is imperative to ensure that people undergoing treatment for LTBI receive the correct dose of Isoniazid.

Thus, the triad for the correct use of a medication composed of: prescription, dispensing and ingestion needs to be monitored and questions related to the professionals who carry out the prescription, to those who participate in the dispensing process, which differs in each service, and also, questions related to drug intake by the patient bring together a new configuration in Tuberculosis programs and will therefore be the object of this study, as described in Figure 1.
[figure not shown]

Figure 1 - Processes related to the triad of evaluation of new dosage

Thus, with the development of the present study, it is intended to understand the process of implementation of the presentation of Isoniazid 300mg for the treatment of LTBI in some health units in different regions of the country in order to identify potential risks in the process of using the drug. medication and ensure patient safety.

To carry out this study, three steps will be adopted that may occur simultaneously. The first stage will be a pragmatic clinical trial with patients LTBI diagnosed in health facilities in Brasília, Curitiba, Florianópolis, Ribeirão Preto - SP and Vitória, which will evaluate the prescription, dispensing and ingestion of the two dosages provided by the PNCT. The second stage will be a cross-sectional study using the 'Knowledge, attitude and practices' methodology to verify compliance in prescribing and dispensing. And the third stage will be a qualitative study with health professionals to analyze the speeches of professionals who prescribe the drug and professionals who dispense the new dosage of 300mg. In this sense, the evaluation of this new presentation will consist of stages that complement each other, as shown in Figure 2:

[figure not shown]

Figure 2. Steps for the Evaluation of Implementation of Isoniazid 300mg for the treatment of LTBI

# OBJECTIVE

• To analyze the occurrence of serious or unexpected adverse reactions resulting from the use of Isoniazid 300mg by the patient for the treatment of latent tuberculosis infection.

• To analyze the patient's use of Isoniazid 300mg for the treatment of latent tuberculosis infection.

• To analyze the information strategies made available to health services on the new presentation of Isoniazid 300mg for the treatment of latent tuberculosis infection.

• To analyze compliance in the prescription of Isoniazid 300mg for the treatment of latent tuberculosis infection through the Knowledge, Attitudes and Practices (CAP) strategy.

•To analyze compliance in the dispensing of Isoniazid 300mg for the treatment of latent tuberculosis infection through the Knowledge, Attitudes and Practices (CAP) strategy.

• To determine the plasma levels of patients undergoing treatment with Isoniazid 100 and 300mg

• To analyze the social representations of health professionals from the basic unit on the use of Isoniazid 300mg for the treatment of latent tuberculosis infection.

• To know the meanings of health professionals at the basic unit about the use of Isoniazid 300mg for the treatment of latent tuberculosis infection.

• To identify the role of health professionals from the basic unit in relation to patients using Isoniazid 300mg for the treatment of latent tuberculosis infection.

• To interpret how health professionals at the basic unit relate their conceptions to the prescription of Isoniazid 300mg for the treatment of latent tuberculosis infection.

• To develop and analyze the use of a computerized system for mobile devices that helps health professionals in the diagnosis and treatment process, as well as to assist in the prevention and care of people with latent Tuberculosis, evaluating its use in these health services to integrate follow-up actions as well as evaluating the degree of solvability of these actions from the system.

# METHODS

STUDY STEPS

First step

Research sites and Study design

This step will be carried out in Brasília, Curitiba, Santa Catarina, Ribeirão Preto, Espírito Santo in the form of a pragmatic, open-label, randomized clinical trial in health units that provide care to patients with Tuberculosis and whether or not they have a Tuberculosis Control Program (PCT acronym in Portuguese). ). The health facilities that prescribe LTBI treatment will be chosen. From June 2018 to March 2019, people over 18 years of age with indication for LTBI treatment will be invited to participate in this study.

After signing the informed consent term, the contacts will be randomized to receive Isoniazid 100mg or 300mg and will be followed up until the end of treatment.

The primary outcome will be the success rate of LTBI treatment in the new 300mg formulation represented by the proportion of subjects with 270 doses of isoniazid between 9 to 12 months.

Secondary outcomes will be evaluated by comparing adverse effects in the two groups (Isoniazid 100mg or 300mg).

**Phase 1- Baseline- before the introduction of Isoniazid 300mg**

Each participant who will receive treatment for LTBI will be guided by the professional responsible for their treatment in relation to taking the medication and possible adverse effects. A medication intake diary containing information about the time of medication intake and the presence of any signs or symptoms of adverse effects will be delivered to the participants through a cell phone application that will be developed for the study. In addition to the diary, this case will be entered into the latent tuberculosis infection treatment reporting system at each research site.

**Phase 2- Follow-up**

Study subjects will be interviewed by the researchers regarding medication intake and adverse effects at the following study periods: week 2, first month, second month, and end of treatment.

Thus, 2 forms will be built, one for diagnosis and another for follow-up (Appendix 1 and 2), based on the forms proposed by the PNCT for the follow-up of these people, already in use in other capitals. The follow-up will also be entered into the notification system for the treatment of latent tuberculosis infection in force in each municipality. The forms will include sociodemographic and clinical information regarding initiation, follow-up and outcome of LTBI treatment. The data can be collected independently in the presence of a data network, whether on cell phones, tablets, notebooks or desktops, if necessary, the data can also be collected in physical media.

In secondary outcomes, in addition, new technologies are being proposed so that the treatment of LTBI can be monitored by health services and so that the health education process, especially applied to TB, can be more easily achieved through an application.

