**SAMPLE SIZE CALCULATION**

For the sample size calculation, the parameters of the primary outcome of adherence to LTBI treatment were used. Non-adherence rates vary between studies from 40 to 20%, with most studies being situated between more than 30% abandonment of LTBI treatment. For the sample calculation, we used an expected dropout rate reduction of around 11%. That is, the expected rate of abandonment of the LTBI treatment expected in the 300mg group would be 19% and in the 100mg group, 30%. With a power of 80% to detect differences and a significance level of 5%, it is estimated that 474 subjects are needed in each group. The STATA 15.0 program was used and a loss of 15% was also considered, this number being corrected for 546 study subjects.

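### After month 2 no researcher interview is scheduled until each participant's own end of treatment, none is tied to abandonment, and time on treatment is expected to differ by arm, which tilts the adverse-effect comparison

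*Protocol*

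**What the plan says.** Phase 2- Follow-up fixes the interviews on medication intake and adverse effects "at the following study periods: week 2, first month, second month, and end of treatment". The METHODS section defines treatment success as "the proportion of subjects with 270 doses of isoniazid between 9 to 12 months" and says that participants "will be followed up until the end of treatment". The last interview therefore has no common date from randomisation.

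Two other sources run alongside. In Phase 1- Baseline, each participant receives a medication diary. It covers intake times and "the presence of any signs or symptoms of adverse effects will be delivered to the participants through a cell phone application". Phase 2 adds: "The follow-up will also be entered into the notification system for the treatment of latent tuberculosis infection in force in each municipality".

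Adverse effects matter to the trial in two ways. One objective is "To analyze the occurrence of serious or unexpected adverse reactions resulting from the use of Isoniazid 300mg by the patient". METHODS adds: "Secondary outcomes will be evaluated by comparing adverse effects in the two groups (Isoniazid 100mg or 300mg". The ANALYSIS PLAN compares proportions by Pearson's chi-square and reports relative risks with 95% confidence intervals. It states no measure per unit of time on treatment.

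On retention, the SAMPLE SIZE CALCULATION assumes that "the expected rate of abandonment of the LTBI treatment expected in the 300mg group would be 19% and in the 100mg group, 30" (per cent).

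**The concern.** There are two separate problems.

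**Recording.** Three interviews fall in the first two months, and the fourth depends on when the participant's treatment ends. If a reaction makes someone stop at month 4, no sentence requires an interview at that point. The researchers may learn of it only if the participant enters it in the diary or the service notifies it. Reactions that lead to stopping are among those that a safety objective most needs to capture.

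**Exposure.** The planned comparison counts participants. The trial's own hypothesis is that people stay on 300mg longer. An arm that takes the drug for longer has more time in which to have an adverse effect. With equal monthly rates, its proportion would tend to be higher. A reader could take this as a tolerability disadvantage of the new tablet when it only reflects better retention.

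**Working it through.** The protocol gives no figure for adverse effects, so there is none to reproduce. Document inputs: interviews at week 2 and months 1 and 2; completion at 9 to 12 months; abandonment *d* = 0.30 (100mg) and 0.19 (300mg). The timing of abandonment and all adverse-effect rates below are assumptions.

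**1. Interview gap for completers.** Gap = month of completion − 2.
- 9 − 2 = 7 months, and 7/9 = 78% of the course.
- 12 − 2 = 10 months, and 10/12 = 83% of the course.

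The gap is shorter for anyone who stops early. The Subanalysis section places the end of treatment at the 6th month, which would give 6 − 2 = 4 months; the two statements of treatment length need to be reconciled. The SCHEDULE closes follow-up in November 2019, about 8 months after the last enrolment at the end of March 2019. For those participants the gap is at most about 8 − 2 = 6 months.

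**2. Time on treatment by arm, 9-month course.** If all abandonment occurs at month *t*, the mean is 9(1 − d) + t·d. With a constant abandonment rate λ = −ln(1 − d)/9, the mean is d/λ.

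| Assumed abandonment | 300mg (months) | 100mg (months) | Ratio |
| --- | --- | --- | --- |
| Constant rate (λ = 0.0234; 0.0396) | 8.11 | 7.57 | 1.07 |
| All at month 2 | 0.81×9 + 0.19×2 = 7.67 | 0.70×9 + 0.30×2 = 6.90 | 1.11 |
| All at month 1 | 0.81×9 + 0.19×1 = 7.48 | 0.70×9 + 0.30×1 = 6.60 | 1.13 |
| Even over months 2 to 9 (mean 5.5) | 0.81×9 + 0.19×5.5 = 8.34 | 0.70×9 + 0.30×5.5 = 7.95 | 1.05 |

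For a 12-month course with all abandonment at month 2, the means are 10.10 and 9.00 months, ratio 1.12.

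**3. Effect on the proportion with an adverse effect.** Assume the same constant rate *h* per month in both arms and no events counted for abandoners after month 2. Then p2 = 1 − e^(−2h), p9 = 1 − e^(−9h), and the recorded proportion is d·p2 + (1 − d)·p9. At h = 0.02, p2 = 0.0392 and p9 = 0.1647.
- 100mg: 0.30×0.0392 + 0.70×0.1647 = 0.127.
- 300mg: 0.19×0.0392 + 0.81×0.1647 = 0.141.
- Ratio 1.109 (1.110 at h = 0.01; 1.106 at h = 0.04).

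**4. How much of that is recording.** If abandoners stop at month 2, nothing on treatment has been missed, and the whole 1.109 is exposure. If they stop evenly over months 2 to 9 and everything is recorded, an abandoner's average risk is 1 − (e^(−2h) − e^(−9h))/(7h) = 0.1034 at h = 0.02. The proportions are then 0.30×0.1034 + 0.70×0.1647 = 0.146 and 0.19×0.1034 + 0.81×0.1647 = 0.153, ratio 1.046. In that pattern, failing to record anything after month 2 in abandoners moves the ratio from 1.046 to 1.109.

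**5. If adverse effects cluster early.** Keep the 9-month risk equal between arms and all abandonment at month 2, with a share *f* of the risk in the first two months. The ratio is (0.19f + 0.81)/(0.30f + 0.70).
- f = 0.50: 0.905/0.850 = 1.065. Divided by the time ratio of 1.112, the ratio per person-month is 0.96.
- f = 0.75: 0.9525/0.925 = 1.030. Per person-month it is 0.93.

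Under early clustering the person-month rate leans the other way, so the two measures should be shown together.

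**The case against.** **Other sources collect adverse effects.** A reader might infer that after month 2 nobody records them until treatment ends. The documents do not support that: every participant has a diary for signs and symptoms, and follow-up is entered in the notification system. This stands, and it narrows the point to researcher interviews. It does not remove it. The diary is self-reported, and the protocol does not say who reviews it, how its entries enter the analysis, or what happens to it after abandonment. That people who abandon also stop filling it in is plausible, but the document does not say so.

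**Abandonment may already count as end of treatment.** Stopping ends treatment, the forms are said to cover treatment outcome, and the appendix forms are not in the text at hand. They may already hold a stop date and reason. This is fair: the supportable defect is an undefined trigger, not proof that no interview will take place.

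**The ratio of 1.11 is not a recording artefact.** A reader might take it as one. Step 4 shows that it can arise with perfect recording, so extra interviews alone would not correct it. The sizes also depend on assumed timing and rates, and early clustering shrinks them. All of this stands, and it is why the recommendation has two parts.

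**Rates per person-month are usually left to an SAP.** Often so. Here, however, the protocol's own ANALYSIS PLAN already fixes a comparison of proportions, and the addition is to that stated choice.

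**The safety objective is not a comparison between arms.** Correct. It concerns 300mg only, and its place at the head of the list is not a ranking. The exposure argument bears on the secondary outcome, and the recording argument on both.

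**Conclusion.** The point holds in a limited form. Interviews after month 2 depend on each participant's end of treatment, 7 to 10 months later for those who complete in 9 to 12 months, and no interview is clearly tied to abandonment. On the protocol's own abandonment rates and an assumed 9-month course, the 300mg arm would be on treatment about 7 to 13% longer in the first three patterns tabulated, and about 5% longer if abandonment is spread evenly over months 2 to 9. At equal constant monthly rates, the proportion with an adverse effect would tend to be about 5 to 11% higher in relative terms on 300mg in the two patterns worked. It would be nearer 3 to 6% if half to three-quarters of the risk falls in the first two months.

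The imbalance is modest and conditional; it is not certain that 300mg will look worse. Nor can the share of stopping-related reactions that would be missed be calculated from the document. The change is still worth making, because it is cheap and protects the named secondary outcome.

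**What to change.** 1. In Phase 2- Follow-up, state that the last interview takes place when treatment stops for any reason, whether completed or abandoned. It should record the date of stopping and whether an adverse effect was a reason. If the follow-up form already has these fields, only the trigger needs adding.
2. In the ANALYSIS PLAN, report adverse effects per person-month on treatment by arm alongside the per-participant proportions and relative risks. Say that diary entries already being collected will be used for events and time on treatment.

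The first change addresses missed reactions and the second addresses unequal exposure; neither does the other's work. The cost is protocol wording, possibly two form fields, and some short calls to people who have left treatment.

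A fixed interview for everyone 12 months after randomisation is not recommended. With follow-up closing in November 2019, it could not be held for participants enrolled after November 2018 unless follow-up were extended.

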**SAMPLE SIZE CALCULATION**

For the sample size calculation, the parameters of the primary outcome of adherence to LTBI treatment were used. Non-adherence rates vary between studies from 40 to 20%, with most studies being situated between more than 30% abandonment of LTBI treatment. For the sample calculation, we used an expected dropout rate reduction of around 11%. That is, the expected rate of abandonment of the LTBI treatment expected in the 300mg group would be 19% and in the 100mg group, 30%. With a power of 80% to detect differences and a significance level of 5%, it is estimated that 474 subjects are needed in each group. The STATA 15.0 program was used and a loss of 15% was also considered, this number being corrected for 546 study subjects.

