**ANALYSIS PLAN**

The explanatory variable of primary interest will be the participant's adherence to LTBI treatment. Other explanatory variables will be used in the analysis models, respecting possible hierarchy and confounding relationships: (1) Demographic and socioeconomic factors: age, sex, place of residence, state capital (yes/no), year of diagnosis, ethnicity or skin color (white, black, brown, yellow and indigenous), formal education (number of school years completed); (2) Pre-existing medical conditions and comorbidities: HIV serology, diabetes, alcoholism and mental illness; (3) Variables associated with infection or adverse effects of LTBI treatment.

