LTBI treatment success and dropout rates will be calculated for each study group. Student's t test will be used to compare means and Pearson's chi-square test will be used to compare proportions and the variables associated with the outcome of interest (p < 0.20) will be included in the multivariate regression model for adjustment. Results are presented in relative risk (RR) with a 95% confidence interval (95% CI). Ideally, all subjects included in the study should complete it following the initial protocol. This situation almost never happens, for different reasons. In general, there are losses, non-adherence to treatments and other deviations from the protocol. For the analysis of the results, two basic populations will be defined: the first is defined by the “intention-to-treat” (ITT) which will include all patients regardless of protocol violations and loss to follow-up; the second, referred to as “per-protocol” (PP), will be a subset of the first, including only patients who completed treatment according to the protocol criteria, excluding all violators. These two analyzes are important, as a significant violation of the criteria established in the protocol (many losses, switching or poor adherence to treatment, and/or other deviations) in the ITT analysis may include a no-difference bias resulting in a lower treatment effect and greater risk of falsely declaring non-inferiority. On the other hand, the PP analysis, in these adverse situations, may include a difference bias, resulting in a greater effect of the treatments and a greater risk of falsely declaring superiority. Therefore, ITT analyzes are conservative for superiority while PP are conservative for non-inferiority. We will therefore present both and the CONSORT Statement will also be used throughout the report (Schulz, Altman and Moher, 2010). All analyzes will be performed in Stata, version 15.0.

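### The primary outcome is stated in conflicting ways, and the 80% power does not clearly apply to 270-dose success under ITT, where power is about 63% to 85% depending on how losses count

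*Protocol*

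**What the plan says.** Four places in the Protocol bear on this point.

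- **Methods, First step.** "The primary outcome will be the success rate of LTBI treatment in the new 300mg formulation", which is "represented by the proportion of subjects with 270 doses of isoniazid between 9 to 12 months". The 100 mg arm is not mentioned in that sentence. The secondary outcome sentence that follows does compare the two groups, on adverse effects.
- **Sample Size Calculation.** "For the sample size calculation, the parameters of the primary outcome of adherence to LTBI treatment were used". The rates used are for abandonment, in per cent: "expected in the 300mg group would be 19% and in the 100mg group, 30". Power is 80% at the 5% level. The result is 474, described as a per-group number, and it becomes 546 after a 15% loss allowance.
- **Analysis Plan, first paragraph.** "The explanatory variable of primary interest will be the participant's adherence to LTBI treatment". The other explanatory variables listed are demographic and socioeconomic factors, comorbidities, and variables linked to infection or adverse effects. Randomised arm is not among them.
- **Analysis Plan, second paragraph.** "LTBI treatment success and dropout rates will be calculated for each study group". Proportions are compared by Pearson's chi-square, and results are given as relative risks. The ITT population is one "which will include all patients regardless of protocol violations and loss to follow-up". A per-protocol analysis is also planned.

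Under Selection of Individuals and Randomization, recruitment is set at 186 participants in Espírito Santo and 90 in each of the other centres.

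**The concern.** There are two linked problems.

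**The outcome.** Completing 270 doses in the window and abandoning treatment are not declared to be complements. Someone who stays in care but takes fewer than 270 doses within 12 months is not a success, yet has not obviously abandoned. The two measures can therefore give different answers, and the Protocol attaches the word primary to both 270-dose success and adherence. Naming adherence as the explanatory variable reverses the roles: in this trial adherence is what is measured and the formulation is what is tested.

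**The power.** An inflation for loss makes sense when lost participants leave the analysis. The ITT population keeps them. The 80% was therefore calculated for one measure in one set of participants, while the stated primary outcome and population are different. If losses count as non-success in addition to abandonment, the gap between arms may narrow and power falls. If they are already part of abandonment, the allowance is a bonus and power rises. A reader cannot tell from the Protocol what chance the trial has of detecting its own target difference.

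**Working it through.** **Inputs.** Abandonment 0.30 (100 mg) and 0.19 (300 mg), power 80%, alpha 5%, and loss 15% come from Sample Size Calculation. Sidedness is not stated, and two-sided is used because it reproduces the plan's number. Recruitment of 186 and 90 per other centre comes from Selection of Individuals and Randomization. Equal allocation is inferred from the balanced blocks described there.

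**Step 1: reproduce 474.** With unpooled variance,

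n per arm = (1.960 + 0.8416)² × (0.30 × 0.70 + 0.19 × 0.81) / 0.11² = 7.849 × 0.3639 / 0.0121 = 236.05, rounded up to 237.

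Twice 237 is 474, so 474 is the total for both arms. The pooled-variance formula gives 239 per arm (478 in total).

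**Step 2: reproduce 546.** 474 × 1.15 = 545.1, taken up to 546. Recruitment agrees: there are five sites, and 186 + 4 × 90 = 546. The trial therefore has 546 participants in total, 273 per arm. The per-group wording in the sample size section contradicts this.

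**Step 3: what the 80% describes.** Power is taken as

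Φ{ [d − 1.96 √(2p̄(1−p̄)/n)] / √[(p₁(1−p₁) + p₂(1−p₂))/n] },

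where d is the difference and p̄ the mean of the two proportions. If 15% are lost and removed, 273 × 0.85 = 232 per arm remain. For 0.70 against 0.81:

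(0.11 − 0.0783) / 0.0396 = 0.80, so power is 78.9%.

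That is close to the nominal 80%, so the stated power fits an analysis that drops the lost.

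**Step 4: the same design under ITT, 273 per arm.** Success among those retained is assumed to be 1 minus abandonment, and a loss is assumed to count as non-success.

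| How losses relate to abandonment | Success, 100 mg | Success, 300 mg | Difference | Power |
|---|---|---|---|---|
| Already inside the 30% and 19% | 70.0% | 81.0% | 11.0 points | 85.0% |
| Separate, 5%, proportional | 66.5% | 76.95% | 10.45 points | 77.5% |
| Separate, 15 points off both arms | 55.0% | 66.0% | 11.0 points | 75.0% |
| Separate, 10%, proportional | 63.0% | 72.9% | 9.9 points | 69.9% |
| Separate, 15%, proportional | 59.5% | 68.85% | 9.35 points | 62.5% |

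In the last row, 0.70 × 0.85 = 0.595 and 0.81 × 0.85 = 0.6885. Then (0.0935 − 0.0804) / 0.0408 = 0.32, which gives 62.5%.

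**Step 5: dependence on the total.** If 546 were a per-arm number, the last row would have 89.8% power. The centre-by-centre recruitment figures do not allow that reading.

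**The case against.** **A reader might infer that the trial simply has 63% power.** The documents do not support that. The figure needs the full 15% lost in each arm, losses scored as failures, losses wholly separate from abandonment and removing successes in proportion, and success equal to 1 minus abandonment among those retained. The sample size section moves freely between non-adherence, dropout and abandonment, which is compatible with the lost already being counted in the 30% and 19%. On that reading power is 85.0%. This objection stands, and 62.5% is only the low end of a conditional range.

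**A reader might infer that no comparison between arms is planned.** That goes too far. The trial is sized on 300 mg against 100 mg, and the Analysis Plan calculates rates in each group and reports relative risks. The single-arm wording in Methods and the reversed roles in the Analysis Plan are errors of statement. The intended comparison can still be recognised.

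**A reader might infer that a lost participant can never show 270 doses.** This is not established. Intake is recorded in an app diary and cases are entered in each site's treatment reporting system (Phase 1), and follow-up is entered in the municipal notification system (Phase 2). A missed research interview need not erase the treatment outcome.

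**The 15% may cover people who really leave the analysis.** Participants transferred two or more weeks after starting treatment are excluded under Selection of Individuals and Randomization. Inflating for them would be coherent, but the sample size section does not tie the 15% to transfers, and the ITT definition retains losses to follow-up.

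**Scoring of losses commonly belongs in a statistical analysis plan.** That is fair, and the lack of such a rule here is not the finding. Nor is sizing on abandonment a defect in itself: if success and abandonment are complements, 70% against 81% and 30% against 19% have the same power. What remains is that the Protocol's own statements of outcome, explanatory variable, loss allowance and population do not fit together.

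**Conclusion.** The concern holds in a limited form. The primary outcome is given as 270-dose success in one place and as adherence, sized on abandonment, in another. In a third, adherence is the main explanatory variable and arm is not listed. An arm comparison is clearly intended all the same.

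The stated 80% corresponds to abandonment after removing the 15% lost (78.9% at 232 per arm). It does not clearly carry over to 270-dose success in a population that keeps everyone. At 273 per arm, that power is 85.0% if the abandonment rates include losses and 75.0% if 15 points are taken from both arms. If losses are separate and proportional, it is 77.5%, 69.9% or 62.5% at 5%, 10% or 15% loss. No single figure is fixed by the documents.

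The range rests on a two-sided 5% test, equal allocation, a total of 546, losses counted as non-success, and no further failures among those who stay in care but miss 270 doses. The Protocol gives no rate for that last group, so its effect cannot be sized.

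**What to change.** 1. In Methods, state one primary outcome: the proportion of randomised participants with 270 doses within 9 to 12 months, 300 mg against 100 mg, analysed by ITT, with participants lacking documented completion from any of the planned sources counted as non-success.
2. In the Analysis Plan, make randomised arm the explanatory variable of primary interest and adherence, as defined in item 1, the outcome. Make dropout a secondary outcome.
3. In Sample Size Calculation, say whether the 30% and 19% already include participants lost to follow-up. If they do, give power as 85% at 273 per arm and explain that the 15% allowance is not needed for ITT. If they do not, give the conditional range down to about 63%, with the assumptions shown.
4. Correct 474 to a two-arm total (237 per arm), and state that 546 is the total randomised.

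The cost is Protocol wording and possibly a less favourable stated power. The correction itself needs no extra patients. Restoring 80% in the least favourable case would be a separate decision, and would need 412 per arm (824 in total).
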